### Trial design

2.1

We will conduct a three-arm RCT to compare the effectiveness, acceptability, and cost-effectiveness of Navigating Burnout in reducing burnout among doctors across three delivery modalities.

Medical doctors (n = 207) will be randomly allocated to receive either [1] a blended version of the program combining the digital Navigating Burnout resources with five fortnightly telehealth sessions with a clinical psychologist [2]; a digital-only, self-guided version of the Navigating Burnout program; or [3] an active attention control where participants will be provided with digital self-care psychoeducation via email each fortnight. Across all conditions the treatment phase across will last 10 weeks.

We will measure self-reported burnout, psychosocial wellbeing, workforce engagement, and workforce attrition intentions before treatment, immediately after treatment, and 3 months after completing treatment (see Fig. 1 for trial design). This design will enable us to examine the effectiveness and acceptability of blended care Navigating Burnout compared to self-guided Navigating Burnout, as well as to examine the effectiveness of self-guided Navigating Burnout relative to an appropriate control.

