In the self-guided arm, participants will be emailed a link to Navigating Burnout to engage with independently over 10 weeks. While participants will have access to the entirety of Navigating Burnout from onset, progress will be supported by fortnightly structured reminders that encourage participants to continue working through the course.

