### Randomisation

2.6

Eligible participants will be randomly allocated to the blended care, self-guided, or active attention control arm using a 1:1:1 ratio. Randomisation will be completed following completion of baseline outcomes.

A randomisation list in a Microsoft Excel file will be prepared in advance using a random number generator using block sizes of 6, 9, and 12. When a participant is ready to be randomised, the list holder will be contacted, and the allocation provided. Participants will be informed which treatment they have been randomly assigned via email.

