### Procedure

2.8

Eligible participants will complete baseline surveys (demographics and psychometrics) before random allocation to self-guided, blended, or active attention control. All arms will access their allocated treatment over 10 weeks. Participants will complete follow-up surveys (psychometrics, service acceptability questions) immediately post-treatment, and again three months post-treatment to assess maintenance of therapeutic effects.

Following completion of the 3 months post-treatment survey, or once participants are considered lost to follow-up at the 3 months post-treatment timepoint, participants allocated to the self-guided or active attention control will be provided with information about TEN, including information on how to access the self-guided Navigating Burnout and/or person-to-person care.

Participants will complete 6 psychometric questionnaires: Oldenburg Burnout Inventory (OLBI; burnout) [22], Depression Anxiety Stress Scale (DASS-21; depression and anxiety) [23], Work and Social Adjustment Scale (WSAS; psychosocial functioning) [24], World Health Organisation Health and Work Performance Questionnaire (WHO-HPQ; workforce participation) [25], Turnover Intention Scale-6 (TIS-6; workforce attrition) [26], and Client Satisfaction Questionnaire (CSQ-8; intervention acceptability) [27]. To further assess acceptability, bespoke questions regarding the self-reported usage and acceptability of Navigating Burnout will also be employed, alongside open-ended questions about participants’ experiences with their allocated treatment and their experiences of burnout.

The OLBI, DASS-21, WSAS, WHO-HPQ, and TIS-6 will be completed at baseline, post-treatment, and 3 months post-treatment, while the CSQ-8 and service acceptability questions will only be completed at the post-treatment timepoint. See Table 1 for an overview of measures employed across trial timepoints. Regular safety audits (2–3 times per week) of the post-treatment and 3 months post-treatment surveys will be conducted, and any responses indicative of distress or suicidal ideation will be reported to PB. If a participant consented to a check-in call related to indicators of distress or suicidal ideation, a clinical psychologist (PB or MB) will contact the participant immediately.

**Table 1 tbl1:** Measures employed across trial timepoints.

Measure	Baseline	Post-treatment	3 months post-treatment

Demographics	X		
OLBI	X	X	X
DASS-21	X	X	X
WSAS	X	X	X
WHO-HPQ	X	X	X
*TIS-6*	X	X	X

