CSQ-8		X	
Self-reported service usage		X	X
Objective service usage		X	X
Open-ended service acceptability		X	
Open-ended burnout	X	X	X

In the blended care arm, participants will be asked to complete an additional OLBI and DASS-21 if their first consultation is arranged for more than three weeks after their baseline survey is completed. This measure will be provided to participants two weeks before their first consultation date. This will ensure the primary outcome remains valid despite delays to treatment start in the blended care arm (e.g., due to treating clinicians being at capacity or participants' availability), as well as provide treating clinicians with updated data on participants’ current mental health.

To aide participant retention, participants will be reimbursed for their participation by means of a $25 digital gift card sent via the GiftPay system to their nominated email at the completion of each measurement point (i.e. baseline, post-treatment, and 3 months post-treatment). To minimise attrition, participants who do not return survey data will receive up to 3 automated survey reminders via email every 2 days from the initial survey invitation date. Those who do not return survey data after 2 weeks past the final automated reminder will receive a final reminder from a member of the research team sent from the trial email account. To further aide engagement in the in the blended care arm, participants will liaise with a member of the research team or patient care coordinator from the Black Dog Institute Clinical Service regarding consultations and attendance (e.g. organising of consultations in a piecemeal manner when a participant cannot commit to all 5 sessions from initial contact due to scheduling issues, rescheduling of cancelled appointments, etc).

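### A repeat OLBI taken after allocation, only in delayed blended-arm participants, cannot keep the primary outcome valid as the protocol claims; the pre-randomisation OLBI should be named as the sole baseline

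*Protocol article*

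**What the plan says.** All references are to the protocol article.

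- **Order of events.** Section 2.6: "Randomisation will be completed following completion of baseline outcomes". Participants are then told their allocation by email. Section 2.8 also places the baseline surveys before allocation in every arm.
- **The extra measure.** Under section 2.8, blended participants complete an "additional OLBI and DASS-21 if their first consultation is arranged for more than three weeks after their baseline survey is completed". On its timing: "This measure will be provided to participants two weeks before their first consultation date". Neither of the other arms has a counterpart, and Table 1 does not list it.
- **Its purpose.** Section 2.8: "This will ensure the primary outcome remains valid despite delays to treatment start in the blended care arm". Giving treating clinicians current data is a second purpose in the same sentence.
- **Follow-up clock.** Section 2.1 times the follow-up surveys "immediately after treatment, and 3 months after completing treatment", and section 2.9 puts the primary endpoint at the later of the two. Section 2.8: "All arms will access their allocated treatment over 10 weeks". In the self-guided arm (section 2.3), "participants will be emailed a link to Navigating Burnout to engage with independently over 10 weeks".
- **Primary analysis.** Section 2.13 specifies a three-arm by two-time mixed ANCOVA (baseline and 3 months post-treatment), adjusted for gender, age, profession and regionality. It has one baseline level and no term for elapsed time.

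**The concern.** The primary comparison is change in OLBI between randomised arms, so baseline has to mean the same thing in each arm. The repeat score differs from the ordinary baseline in three ways: it follows allocation, its takers know they will see a psychologist, and they are selected by clinician capacity or their own availability. Yet the protocol says this score secures the primary outcome. The natural way for it to bear on a baseline-to-3-month change is as a substitute baseline. Any early change (spontaneous recovery, regression to the mean, reaction to allocation) would then be dropped from part of one arm and kept in the other two. DASS-21 would be affected in the same way, while WSAS, WHO-HPQ and TIS-6, which are not repeated, would keep their original baseline.

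Keeping the original baseline avoids that problem but leaves a second one. A delayed start combined with follow-up counted from the end of treatment stretches the interval from randomisation to endpoint in the blended arm. The repeat OLBI does nothing to equalise that interval between arms.

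**Working it through.** The plan gives no figure on this point to reproduce. The check sets out the timeline and then shows an assumed range.

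**1. Timeline.** Inputs from the document: 10 weeks of treatment, follow-up 3 months after it (taken as 13 weeks), repeat OLBI 2 weeks before the first consultation. Let d be the weeks from baseline to first consultation, with d > 3 in triggered participants. Assumed, because it is not stated: the blended 10 weeks start at the first consultation, and the digital arms start about when baseline is taken.

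| | Weeks to primary endpoint |
|---|---|
| Digital arms, from baseline | 10 + 13 = 23 |
| Delayed blended, from original baseline | d + 10 + 13 = 23 + d |
| Delayed blended, from repeat OLBI | 2 + 10 + 13 = 25 |

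The repeat falls d − 2 weeks after baseline, so more than 1 week after it. Neither choice of baseline gives delayed blended participants the same baseline-to-endpoint contrast as the other arms. With the original baseline the interval is longer; with the repeat the interval is nearly matched but the starting score is post-randomisation.

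**2. Illustrative size with no treatment effect.** All inputs are assumed: natural decline g = 0.005 to 0.03 SD per week, d = 4 or 8 weeks, share of the blended arm delayed p = 0.3 to 1.0.

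- *Original baseline kept.* Extra blended decline = p × g × d. Lowest: 0.3 × 0.005 × 4 = 0.006 SD. Highest: 1.0 × 0.03 × 8 = 0.24 SD. This favours blended.
- *Repeat used as baseline, steady decline.* The blended baseline moves down by p × g × (d − 2), from 0.3 × 0.005 × 2 = 0.003 to 1.0 × 0.03 × 6 = 0.18 SD. What remains in the change score is p × g × d − p × g × (d − 2) = 2 × p × g, from 0.003 to 0.06 SD, still slightly in favour of blended.
- *Repeat used as baseline, regression to the mean.* If entrants lie m SD above their usual level and the short-term correlation is r, the repeat falls by (1 − r) × m. With m = 0.5 to 1.0 and r = 0.8 to 0.9, that is 0.1 × 0.5 = 0.05 to 0.2 × 1.0 = 0.20 SD in delayed participants. Over the arm (times p) it is 0.3 × 0.05 = 0.015 to 1.0 × 0.20 = 0.20 SD, and it works against blended.

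If burnout rises during the wait, the drift terms reverse. The net sign is therefore not determined.

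**3. What a given bias would do.** The plan's 69 per arm with 30% attrition leaves 69 × 0.70 = 48.3, so n = 48. For bias b and pre-post correlation ρ, the shift in the test statistic is b / (√(2(1 − ρ)) × √(2/n)). Two-sided 5% pairwise false-positive rates (normal approximation):

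| b (SD) | ρ = 0.5 | ρ = 0.7 |
|---|---|---|
| 0.02 | 0.051 | 0.052 |
| 0.08 | 0.068 | 0.080 |
| 0.16 | 0.123 | 0.173 |
| 0.24 | 0.217 | 0.329 |

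With few or short delays the effect is negligible. With a fully delayed arm and fast drift it could alter the conclusion.

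**The case against.** The strongest reply is that no sentence says the repeat score replaces baseline. Sections 2.6 and 2.8 place baseline before allocation, Table 1 has a single baseline column that omits the extra measure, and section 2.13 speaks only of baseline. The ordinary reading keeps the original OLBI, and how an auxiliary score enters the analysis is often left to the SAP. This stands as far as it goes: re-baselining is an inference. It does not rescue the validity statement, which the protocol makes positively and puts ahead of the clinician-information purpose.

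A reader might infer several stronger things that the document does not support:

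- *That the blended effect would be understated by a definite amount.* The share delayed, the length of delay and the drift are all unknown. Under steady decline, re-baselining leaves a small overstatement (25 against 23 weeks). Understatement needs front-loaded improvement or regression to the mean, and entry is on self-reported burnout with no stated OLBI threshold.
- *That the biases could never be separated.* The pre-randomisation OLBI is scheduled for every participant, so change can be computed from it, and survey dates allow the timing to be examined.
- *That every triggered participant is assessed at least three weeks later than the digital arms.* The trigger counts from the baseline survey, the lag to start in the digital arms is not given, and no calendar weeks from randomisation are stated.
- *That timing follow-up from the end of treatment is an error.* It gives each arm the same post-treatment interval, which suits the stated interest in maintenance of effect. Timing from randomisation instead would measure delayed participants less than 3 months after treatment. That is a trade-off.

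**Conclusion.** The point holds in a limited form. The protocol gives a post-allocation score, collected in a scheduling-selected part of one arm, a role in securing the primary outcome that such a score cannot perform. If it were used as the ANCOVA baseline, the randomised comparison of change would be compromised. If it is not so used, the stated reason for collecting it is wrong.

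Separately, delayed blended participants are likely to reach the primary endpoint later after randomisation than the digital arms. This is inferred from the end-of-treatment anchor together with the delays that the protocol itself expects; the amount is not stated. The size and net direction of any bias cannot be obtained from the document. The ranges above only show that it could be trivial or material, depending on how many participants wait and for how long. The problem concerns delayed participants and not the whole blended arm by default.

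**What to change.** 1. State that the pre-randomisation OLBI is the baseline in all three arms for the primary analysis.
2. Remove the statement that the repeat OLBI secures the validity of the primary outcome. Limit the repeat to clinician information, an auxiliary variable for imputation, or a sensitivity analysis labelled as such.
3. Record the interval from randomisation to each survey, report it by arm, and add a sensitivity analysis of the primary outcome that accounts for it.

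Two design changes are options for the sponsor to weigh and not required corrections: timing the primary OLBI from randomisation in every arm, which shortens the post-treatment interval for delayed participants; or randomising only once a consultation slot is available, which moves any wait ahead of randomisation for all arms.

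The cost of items 1 to 3 is a change of wording, one recorded interval and slightly more analysis work.

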### Primary outcome

2.9

The primary outcome will be self-reported burnout, as measured by the OLBI, with the primary endpoint being 3 months post-treatment.

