### Sample size

2.12

We will enrol 207 participants to complete the trial. This sample size is sufficient to examine the primary outcome using repeated measures ANOVA of whether the blended care version of the Navigating Burnout program leads to significantly lower burnout between baseline and 3 months post-intervention compared to self-guided treatment based on a power analysis (α = .05 and power = 0.80) using a conservative medium effect size of f = 0.25 between groups estimating a sample size of 53 per arm (WebPower). As there is limited literature on the effect of blended care treatments for burnout relative to self-guided digital psychotherapeutic programs, a medium effect size of f = 0.25 was chosen as a minimum clinically meaningful effect [28]. Accounting for a conservative estimate of 30% attrition based on previous research health professionals [19], 69 participants are required in each arm leading to a total sample size of 207.

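### The last contact with survey non-responders includes no reduced, OLBI-only request, so some 3-month primary outcome data may be lost that a short form could capture

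*Protocol article*

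**What the plan says.** The Primary outcome section names "self-reported burnout, as measured by the OLBI, with the primary endpoint being 3 months post-treatment". Table 1 and the Procedure section place the OLBI in the 3-month survey with the DASS-21, WSAS, WHO-HPQ and TIS-6, usage items and open-ended burnout questions.

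The Procedure section describes the follow-up of non-responders in operational detail. There are up to three automated emails, two days apart. After those, "Those who do not return survey data after 2 weeks past the final automated reminder will receive a final reminder", sent by a team member from the trial's email account. A $25 gift card is paid on completing each measurement point. No shorter form is described for someone who has not answered by then.

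The Sample size section uses an effect size stated as "using a conservative medium effect size of f = 0.25 between groups estimating a sample size of 53 per arm (WebPower". It then says: "Accounting for a conservative estimate of 30% attrition based on previous research health professionals [19], 69 participants are required in each arm", for a total of 207. Under Statistical methods, more than 5% missing 3-month OLBI triggers missingness comparisons, best-worst and worst-best case analyses, last observation carried forward, and a choice between complete-case analysis and multiple imputation.

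**The concern.** The outcome that decides the trial is one short instrument, and the request for it is bundled with everything else. A burnt-out doctor who has ignored four emails about a survey might still answer one questionnaire. As described, the plan never makes that smaller request.

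Missing 3-month OLBI does two kinds of harm. It lowers power, and it makes the result depend on imputation and on the bounding analyses. If non-response is related to burnout itself, which is plausible but not shown in the documents, imputation from observed data would not fully repair the result. Each additional observed OLBI reduces both problems.

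**Working it through.** **Inputs.** From Sample size: α = 0.05, target power 0.80, f = 0.25, 53 completers per arm, 30% attrition, 69 enrolled per arm. From Randomisation: 1:1:1 allocation. The share r of non-responders who would return an OLBI-only form is not in the documents. It is assumed here to lie between 0% and 50%.

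**The plan's own figures.** Take a between-arm F test with k groups and total N, noncentrality λ = N·f², degrees of freedom k − 1 and N − k.
- With k = 3 and f = 0.25, power first reaches 0.80 at N = 158, which is 53 per arm. Power at N = 159 is 0.805. The 53 is therefore reproduced as a three-arm test.
- With k = 2 the same formula needs 64 per arm, so 53 is not the size for the blended versus self-guided comparison alone.
- 53 × 1.3 = 68.9, so 69 is reproduced as multiplication by 1 + 0.30. Dividing gives 53 / 0.7 = 75.7, so 76 per arm.

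**Completers at the planning allowance.** 69 × 0.70 = 48.3 per arm with the OLBI, and 69 × 0.30 = 20.7 without.

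**Recovery that would restore 53.** (53 − 48.3) / 20.7 = 0.227, so about 23% of non-responders, or roughly 5 per arm. Equivalently, loss would have to be no more than 1 − 53/69 = 23.2%.

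**Effect of a short form.** Completers per arm are n(r) = 69 × [1 − 0.30 × (1 − r)]. Three-arm power uses N = 3n, and two-arm power uses N = 2n with d = 2f = 0.5.

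| Assumed recovery r | Loss | Completers per arm | Three-arm power | Two-arm power |
|---|---|---|---|---|
| 0% | 30% | 48.30 | 0.764 | 0.682 |
| 10% | 27% | 50.37 | 0.783 | 0.700 |
| 20% | 24% | 52.44 | 0.800 | 0.718 |
| 30% | 21% | 54.51 | 0.817 | 0.735 |
| 50% | 15% | 58.65 | 0.846 | 0.766 |

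For comparison, 53 per arm gives 0.805 (three-arm) and 0.722 (two-arm).

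Even at 50% recovery, loss would be 15%, still above the 5% that triggers the missing-data analyses. A short form would reduce the dependence on those analyses but would not remove it.

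**The case against.** The strongest reply is that the Procedure section contains no error. It offers an incentive, repeated reminders and a personal last contact, and Statistical methods plans for missing data. A short form is then only a retention idea, with a gain that nobody can read from the documents. Much of this stands. The plan does not contradict itself here, recovery could be close to zero, and the range above has to include zero.

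Several stronger readings are tempting and are not supported:
- **That 30% of primary data will be lost.** The article calls 30% a conservative estimate. It is a sizing allowance and not a forecast for the 3-month visit.
- **That the last email insists on the whole survey.** The text speaks only of survey data and does not say what the email asks for. The whole survey is the natural reading, because no other form is described for that visit, but it is an inference.
- **That anyone who will not finish the battery gives no OLBI.** That would require the OLBI to come late or partial responses to be discarded. The article says neither. A condensed article may leave item order and the handling of partial records to the full protocol, so their absence is no finding.
- **That the reminders cause the shortfall against 53.** The gap between 48 and 53 exists because 53 was multiplied by 1.3 instead of divided by 0.7.

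A short form also has a cost. Its users would give no secondary outcomes at that visit. They would also give no DASS-21 to the safety audit of survey responses that the Procedure section describes. Against that, a person who returns nothing gives the audit nothing either.

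The reply does not dispose of the main point. The article fixes the non-responder sequence down to intervals and sending account, so a change to its last step concerns a stated procedure. The trial already sends a form with only the OLBI and DASS-21 to blended-arm participants whose first consultation is delayed, so a reduced form fits its practice.

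**Conclusion.** The point holds as a cheap improvement to a stated procedure. The article describes only email reminders for survey data and no reduced request for the primary outcome at the last contact, so some 3-month OLBI data may be lost that a short form could capture.

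The size is uncertain. If loss reaches the 30% allowance and 0% to 50% of non-responders return an OLBI-only form, completers per arm go from 48 to 59. Three-arm power at f = 0.25 goes from 0.76 to 0.85, and two-arm power at d = 0.5 from 0.68 to 0.77. Recovery of about 23% would bring the trial back to its own 53 per arm. These figures rest on the assumed recovery range, on equal loss across arms, and on an unadjusted between-arm comparison at one time point. If actual loss is below 30%, there is less to recover.

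The inflation to 69 instead of 76 per arm is a separate defect and should be corrected in its own right. It makes better capture of the OLBI more useful, but the reminder procedure did not create it.

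**What to change.** In section 2.8, state that the final personal reminder for the 3-month survey, worded identically in all three arms, offers the full survey and, for those who will not complete it, an OLBI-only REDCap form that still earns the gift card. The full survey stays the first choice, so that secondary outcomes are given up only by people who would otherwise probably return nothing.

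The sponsor should also state how the short form fits with the safety audit of survey responses, since it carries no DASS-21. The report should give, by arm, the number of primary outcomes obtained by short form.

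The cost is one short REDCap form, a revised reminder text and possibly a minor ethics amendment. No extra enrolment or staff is needed, because the personal email is already planned.
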